**Table 2 Tab2:** **Example of random allocation for two states**

PANEL A: generating the random allocation sequence of “Winning Digits”						
**Lottery 3/1/2011**		**Lottery 2/22/2011**				
**Number**	**Prize (millions)**	**Number**	**Prize (millions)**			
23862	5	36625	5			
19186	0.4					
54595	0.2	Sort order (ascending)				
02437	0.08	3				
09502	0.08	6				
42585	0.08	2				
45776	0.08	5				
**PANEL B: randomization of municipalities**						
**ID**	**State**	**Municipality**	**FISM transfer (millions)**	**“Ticket” Digits**	**ASF**	**EFSL**
07022	Chiapas	Comitán de Domínguez	69	0-1		
07028	Chiapas	Chenalhó	61	2-3	1	
07076	Chiapas	Ocozocoautla de Espinosa	68	4-5		1
07092	Chiapas	San Cristóbal de Las Casas	65	6-7		
07111	Chiapas	Tecpatán	59	8-9		
08012	Chihuahua	Carichí	12	0-1		
08021	Chihuahua	Delicias	15	2-3	1	
08030	Chihuahua	Guazapares	11	4-5		
08032	Chihuahua	Hidalgo del Parral	13	6-7		
08066	Chihuahua	Uruachi	13	8-9		1

The sequence of random numbers from Panel A is: 23862, 19186, 54595, 42585, 02437, 45776, 09502. We use the first 17 winning digits to allocate one municipality by state to an audit by ASF. For example, the first winning digit in the random sequence is a 2. Because Chenalhó was allocated that “ticket” (see Panel B, Digits column), it is selected to be audited by ASF. The second winning digit in the random sequence is a 3, and so Delicias is selected, and so on for the remaining 15 states. To allocate EFSL we begin at the top again, starting with the 18^th^ digit in the random sequence, a 5. Accordingly, Ocozocoautla de Espinosa is allocated to EFSL, and so on. Had the 18^th^ digit been a 2 or a 3, we would have skipped that digit, moved to the next digit different from 2 or 3, and used that digit to allocate the first municipality to EFSL. One municipality cannot be assigned to both ASF and EFSL.

The method of randomization adopted is transparent, replicable, and verifiable. In addition, the only software requirements are a web browser (to access the lottery numbers) and Microsoft Excel. These features were key for the ASF to accept the procedure. However, the lottery numbers span the range 00000 to 59999. Accordingly, the first digit of every winning lottery number can only take the values 0 through 5 while all other digits that can take values from 0 to 9. Thus, the fourth and fifth municipalities in the first state of our study have in practice zero chance of being audited by the ASF because they hold “tickets” (6,7) and (8,9) respectively. After the first assignment, this happens every fifth assignment, when a new lottery number is added to the sequence of “winning digits”. In other words, the randomization procedure generates known non-uniform probabilities of treatment in a subset of the blocks. Only 4 assignments to ASF and 3 to EFSL are affected by the non-homogeneous randomization. Even so, because the probabilities of assignment are known exactly we can adjust randomization hypothesis tests and use inverse probability weighting for estimates. Municipalities assigned to an audit are audited as usual by the assigned federal or state auditor [42]. Figure 1 provides a schematic layout of a municipal FISM audit process.

**Figure 1 Fig1:**
[figure not shown]
**Flow chart of Superior Federal Auditor’s audit process.** Flow chart depicting the Superior Federal Auditor’s (ASF) audit process of municipal expenditures under the federal Contribution Fund for Social Infrastructure (FISM) grant program [43]. Highlighted in grey are ASF judgements, opinions, and outputs.

### Outcome measures

The primary outcome measures of this study capture the effectiveness of the national program of audits amongst the study group. Primary outcomes follow an expected causal order, going from how audits may affect subjects’ beliefs about future audits, to how they modify subjects’ knowledge of program rules, investment preferences, awareness of capacity limitations, compliance with reporting requirements, and the actual allocation of investments between outlying settlements and the council seat (see Table 1). Secondary outcomes compare the effectiveness with which the federal and state level auditors uncover wrongdoings; the severity with which they judge them; and the diligence with which they pursue wrongdoings. (If solid evidence of differences is found, we will do some additional exploratory work, like subgroup analysis by stratifying on the basis of an institutional quality index [44]). Tertiary outcomes explore possible interactions between audits and local accountability systems. We do so by comparing how audits may affect subject’s expectations about future political appointments, career prospects, perceive their principals differently, and whether state governors engage in clientelist practices to blunt the effect of audits on municipalities of their same political persuasion. Due to their specificity most outcome measures were defined and measured by the investigators using a proprietary survey, and related measurement instruments. Specific definitions, measurements, and sources are described in Additional file 2.

Our outcome data come from routine audit reports, other official sources, direct observations by the investigators, and from a proprietary survey of municipal administrators. The survey was developed by the investigators and implemented by the Mexican survey firm *Data Opinion Publica y Mercados*. The survey firm was blind to treatment status. The survey was pilot tested on four municipalities similar to the ones in the experimental group, and the results where used to clarify the meaning of questions and adapt the length of the survey, as well the contact strategy. The survey was fielded over the phone between April 27, 2012 and June 7, 2012. We administered the survey to key personnel in each municipality, including: the Municipal President, Treasurer, Director of Public Services, Director of Public Works, and/or Director of Urban Planning. It was not always possible to contact the personnel, in which case we moved down the municipal hierarchy. Given the sample size of this study, strenuous efforts were made to ensure full response. A copy of the survey is included in Additional file 3. Data from official sources will be collected by a research assistant according to guidelines provided by the researchers. Some data will be collected through direct observations (e.g. does municipality have a web page) according to a measurement instrument developed by the researchers and implemented by a research assistant. Collection of these data is expected to end on January 30, 2013. The research assistant is blind to treatment status. Finally, most outcomes of interest are subjective in nature. This introduces some well known limitations.

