### Attrition

Attrition and missing outcomes can undo the benefits of randomization as observed outcomes may no longer be representative of the full experimental population nor comparable across observed experimental arms [53]. Due to small sample size we tried to prevent attrition by intensive follow up of non-respondents. We also collected logs of call efforts from the survey firm, under the assumption that those hardest to reach are similar to those never reached. We will also try to fill in missing response covariates (e.g. age, gender, and career history of of municipal official) using publicly available information. At the analytical stage we will do the following: Diagnosis: We will report the prevalence of attrition across experimental arms and check the covariate profiles of units missing outcomes versus those reporting outcomes. We will also check how observed outcomes vary with the recorded logs of call efforts.Hypothesis test: We will test the sharp null of no effect of treatment on attrition. Failure to reject the null that the treatment has no effect on the attrition strongly suggests that the observed units are at least comparable across treatment arms [53].Imputation: If the null is rejected then a complete data analysis is only appropriate if the outcome does not cause attrition and the only cause in common between the outcome and the attrition is the treatment [53]. This is a strong assumption. For robustness we will draw inferences using extreme bounds, and consider trimmed bounds, multiple imputations and inverse probability weights analyses as secondary analyses.

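### When junior staff answer for officials who cannot be reached, the attrition check as written can miss it, and survey results may mix who answered with what the audit changed

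*Protocol article*

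**What the plan says.** Under Outcome measures, the protocol article describes a telephone survey of key personnel: the Municipal President, "Treasurer, Director of Public Services, Director of Public Works, and/or Director of Urban Planning". It continues: "It was not always possible to contact the personnel, in which case we moved down the municipal hierarchy". No limit on rank is stated, and the article stresses the effort made to obtain complete response.

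Under Attrition, the plan has three steps.

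- **Diagnosis.** Report attrition by arm and "check the covariate profiles of units missing outcomes versus those reporting outcomes". Call-effort logs are also used: "We will also check how observed outcomes vary with the recorded logs of call efforts".
- **Test.** "We will test the sharp null of no effect of treatment on attrition". Non-rejection, the article says, "strongly suggests that the observed units are at least comparable across treatment arms".
- **Imputation.** This step opens with "If the null is rejected then a complete data analysis is only appropriate if the outcome does not cause attrition" and goes on to extreme bounds, with trimmed bounds, multiple imputation and inverse probability weighting as secondary analyses.

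For respondents' age, gender and career history, the plan is: "We will also try to fill in missing response covariates". Nothing in the text shown compares respondent rank or substitution between arms.

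**The concern.** Who answers the telephone is settled after assignment. The Blinding section says that municipal staff know whether they are being audited, so the availability of senior officials could respond to the audit even though the survey firm was blind. Rank plausibly matters for knowledge of grant rules (H4), awareness of capacity gaps (H6) and political or career expectations (H11, H12). The other survey hypotheses (H1-H3, H5, H13) are exposed in the same way. Outcomes taken from official records or direct observation are not.

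The attrition rule works least well where fieldwork was most successful at filling places. The more substitutes were found, the fewer outcomes are missing, the less likely the attrition null is to be rejected, and the more firmly the stated rule concludes that the arms are comparable. The bounds, which follow on from rejection, are then less likely to be used. Aggregating to municipal level, which Statistical methods plans as a robustness check, does not help, because the same respondents feed the aggregate.

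**Working it through.** **Design count.** 17 blocks × 5 = 85 municipalities. The 1:1:3 ratio gives 17 federal, 17 state and 51 control, as the article states. Pooling the audit arms gives 34 versus 51. No power, response rate or substitution rate is stated, so everything below on size rests on assumed inputs.

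**Logic.** Let r_T and r_C be the proportions of places filled by substitutes in the audited and control arms, and g the mean difference in outcome between a substitute and the intended official. With no effect on any given official, the expected difference between arms is

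shift = (r_T − r_C) × g.

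If r_T = r_C the shift is zero. If every place is filled, a test on missing outcomes sees 0% attrition in both arms and cannot reject, whatever r_T − r_C is.

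**Size.** Take g = 0.5 SD (assumed).

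- 20-point difference: 0.20 × 0.5 = 0.10 SD
- 40-point difference: 0.40 × 0.5 = 0.20 SD

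Standard error in SD units, ignoring blocks and weights, with one value per municipality: √(1/34 + 1/51) = 0.221. The shift is therefore 0.10/0.221 = 0.45 to 0.20/0.221 = 0.90 standard errors.

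**Simulation.** Assumptions: three respondents per municipality, intraclass correlation 0.2, 20% substitution in control, substitutes scoring 0.5 or 1.0 SD lower, no missing outcomes, and no effect on any given official. There were 10,000 runs, each with a Welch t-test on municipal means at two-sided 5%. This is not the trial's own randomization test, and blocks are ignored.

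| Substitution, audited v control | Shift (SD) | Rejection, 34 v 51 | Rejection, 17 v 51 |
|---|---|---|---|
| 20% v 20% | 0 | about 5% | about 5% |
| 30% v 20% | −0.05 to −0.10 | 6–10% | 6–7% |
| 40% v 20% | −0.10 to −0.20 | 10–24% | 8–15% |
| 50% v 20% | −0.15 to −0.30 | 16–45% | 11–29% |

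The negative sign follows only from assuming that substitutes score lower.

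**Could a test on substitution settle the matter?** Power at two-sided 5%, with one respondent per municipality:

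| Substitution, audited v control | 34 v 51 | 17 v 51 |
|---|---|---|
| 30% v 20% | 19% | 15% |
| 40% v 20% | 52% | 39% |
| 50% v 20% | 83% | 66% |

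A non-significant result would not show that substitution was balanced.

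**How wide would extreme bounds be?** For a yes/no outcome the width is r_T + r_C once substitutes are counted as missing. At 40% v 20% that is 0.40 + 0.20 = 0.60, a range of 60 percentage points.

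**The case against.** The strongest reply is that the article is a summary. The detailed analytical plan is Additional file 2, which is not shown, and it could code respondent post or count attrition per intended official. The Attrition text does not fix whether a unit is a municipality or an official, and it also speaks of non-respondents and people never reached. A reader might infer that the attrition test can never detect substitution. The text does not support that. It supports only that the rule, as written, can miss it.

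A reader might also infer that the survey results are biased, or that a rank difference would be taken for an audit benefit. Neither follows. No substitution rate or imbalance is documented, and equal substitution produces no difference between arms. If audits made senior staff harder to reach and substitutes knew less, audited municipalities would score lower on knowledge, which works against H4 and would mask an effect. The sharp-null test on assignment also stays valid: if assignment changes who answers, the measured municipal outcome really has changed. The harm lies in reading that change as one in officials' knowledge or beliefs, and in the inference that the arms are comparable.

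There are partial safeguards. The survey firm was blind, which limits differential effort by interviewers. Call effort should be associated with substitution, and respondent covariates are to be filled in. What stands is that none of these, as described, compares respondent rank by arm, while the article draws a strong conclusion from a test that need not register substitution.

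**Conclusion.** The point holds as a conditional weakness in a stated rule. The article records that substitution took place, and its attrition step can pass over it and still conclude that the arms are comparable. If substitution differs by arm and rank affects answers, H1-H6 and H11-H13 would combine two different changes, in an unknown direction. On the assumed inputs the shift is 0.10 to 0.20 SD, roughly half to nine-tenths of a standard error for 34 versus 51 municipalities. It would be smaller if substitution differed by less than 20 points, and nil if it did not differ. The documents neither show nor rule out an imbalance. It is worth correcting because the stated rule draws reassurance it has not earned.

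**What to change.** Extend the attrition step in three ways.

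1. Define a substitute as a respondent outside the five posts named under Outcome measures. That list is open-ended in the article, so fix it for this purpose. Report respondent post and substitution by arm; the full distribution of posts also shows shifts among the listed posts, which the definition alone would not catch.
2. Apply the planned randomization test of the sharp null to substitution as well as to missing outcomes.
3. Whatever that test shows, repeat the survey hypotheses (H1-H6, H11-H13) as a sensitivity analysis with substitutes treated as missing: once restricted to the listed posts, and once with the planned trimmed and extreme bounds. Interpret the main survey results alongside these.

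The cost is a little more analysis and no new fieldwork, provided that respondent post was recorded, which the article does not say. The bounds will be wider, and the extreme bounds may be uninformative at this sample size. The restricted analysis still selects on a post-assignment event, so it shows sensitivity and does not replace the main analysis.

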**Methods/Design:**

The AUDIT study is a block randomized, controlled, three-arm parallel group exploratory trial. A convenience sample of 5 municipalities in each of 17 states in Mexico (*n*=85) were block randomized to be audited by federal auditors (*n*=17), by state auditors (*n*=17), and a control condition outside the annual program of audits (*n*=51) in a 1:1:3 ratio. Replicable and verifiable randomization was performed using publicly available lottery numbers. Audited municipalities were included in the national program of audits and received standard audits on their use of federal public service infrastructure grants. Municipalities receiving moderate levels of grant transfers were recruited, as these were outside the auditing sampling frame – and hence audit program – or had negligible probabilities of ever being audited. The primary outcome measures capture compliance with the grant program and markers for the causal mechanisms, including deterrence and information effects. Secondary outcome measure include differences in audit reports across federal and state auditors, and measures like career concerns, political promotions, and political clientelism capturing synergistic effects with municipal accountability systems. The survey firm and research assistants assessing outcomes were blind to treatment status.

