## Methods/Design

### Trial design

The AUDIT study is a block randomized, three-arm parallel group, exploratory trial on a convenience sample of 85 municipalities in Mexico. Blocking was done by state across 17 states, with five municipalities per block. Using non-uniform random assignment and a 1:1:3 blocking ratio we assigned one municipality per block to be audited by the ASF, another by the EFSL, and the remaining three municipalities to the control condition (no intervention). Our reporting of the trial design follows the CONSORT 2010 Checklist [39, 40] (See Additional file 1). The trial received an ethics approval by Yale University’s Human Subjects Committee (ref: 1106008610), and is registered with the International Standard Randomised Controlled Trial Number Register (ISRCTN22381841) and the Experiments in Governance and Politics Network (No:20121031). All end line survey participants are required to give informed consent.

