### Blinding

Whereas researchers and ASF management in Mexico city are fully aware of treatment allocations, the survey firm and research assistants collecting outcome data were kept blinded to the allocation. The researchers took no specific measures to ensure field auditors carrying out the audits were blinded to the allocation. Similarly, municipal staff are clearly aware whether they are being audited or not, but there is not reason to expect them to know they are part of an experiment. Finally, because the researchers are not blind to the allocation they will carry out the data analysis according to the detailed analytical plan in Additional file 2.

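### The unqualified statement that research assistants are blind to treatment cannot hold for outcomes taken from audit reports (H9 and H10), and the text leaves open whether blinding was kept for H7 and other assistant-collected outcomes.

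*Protocol article*

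**What the plan says.** The protocol article makes the blinding claim in three places, each time without exception.

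- Outcome measures: "The research assistant is blind to treatment status".
- Blinding: "the survey firm and research assistants collecting outcome data were kept blinded to the allocation".
- Abstract, Methods/Design: "The survey firm and research assistants assessing outcomes were blind to treatment status".

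On where the data come from, Outcome measures says: "Our outcome data come from routine audit reports, other official sources, direct observations by the investigators", followed by the survey of administrators. The word 'other' places audit reports among the official sources. The section continues: "Data from official sources will be collected by a research assistant according to guidelines provided by the researchers". Direct observations, with the existence of a municipal web page as the example, are made "according to a measurement instrument developed by the researchers and implemented by a research assistant".

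On the treatment, the Trial design section says "we assigned one municipality per block to be audited by the ASF, another by the EFSL", with the remaining three municipalities in each block as controls. H9 and H10 in Table 1 compare the two kinds of auditor on the number of observations, refunds to the federal treasury, and severity. The abstract describes this secondary outcome as differences in audit reports between federal and state auditors.

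**The concern.** In this trial the treatment is to be audited, and the two active arms differ by who audits. An audit report is therefore both an outcome document and a record of treatment. Whoever extracts data from it learns that the municipality was audited and by whom. The stated blinding is thus a property that the design cannot have for H9 and H10.

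What is at stake goes somewhat beyond wording. The researchers know the allocation and also run the analysis, so blinded outcome collection is one of the main safeguards left for outcomes that compare audited with control municipalities. H7, on reporting and data accessibility, is close to the study's headline question of compliance. If the person who reads the audit reports also codes H7, and reads the reports first, that safeguard may be gone for H7 as well.

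**Working it through.** The article gives no figure to reproduce. The check has two parts.

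**Setting the statements side by side**

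1. Audit reports are one of the official sources (Outcome measures).
2. A research assistant collects the official-source data (same section).
3. The research assistant is blind to treatment status (same section; repeated in Blinding and in the abstract).
4. Treatment status is whether, and by whom, a municipality is audited (Trial design; Randomization and interventions).

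Statements 1, 2 and 4 together contradict statement 3 for every outcome read from an audit report. Even an assistant who has been told nothing about the trial has the audit status in view.

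**How far the reports reveal the assigned arm**

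Inputs: 17 ASF + 17 EFSL + 51 control = 85 municipalities. The Non-compliance section adds that two municipalities could not be audited, and that state auditors may carry out extra audits outside the national program; it gives no number for these.

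Rule: read the arm from the report's issuer, and read 'control' where there is no report. This assumes that the reader has the list of study municipalities alongside the reports.

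- *Assumption A: both unaudited municipalities were assigned to audit, and no control was audited.* Reports: 17 + 17 − 2 = 32. No report: 85 − 32 = 53, of which 51 are controls. Correctly read: 32 + 51 = 83, and 83/85 = 97.6%.
- *Assumption B: as A, but five controls (a number chosen for illustration) had an extra state audit.* Those five are misread as EFSL. Correctly read: 83 − 5 = 78, and 78/85 = 91.8%.
- *Reference: always guess 'control'.* 51/85 = 60%.

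The reports show the treatment received. Under either assumption, that comes close to showing the treatment assigned.

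**Which other outcomes could be affected**

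Carry-over needs two conditions: the same person extracts the reports and codes the other outcomes, and the reports are opened first. On the first, Outcome measures moves from 'a research assistant' for each task to 'the research assistant', which suggests one person; Blinding and the abstract use the plural. On the second, no order is given. The outcomes exposed if both conditions hold are those an assistant takes from official sources or by direct observation: chiefly H7, possibly H8 and H14. Survey outcomes were collected by a separate, blinded firm and are not affected.

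**The case against.** The strongest reply is that the consequence is small. H9 and H10 have no control arm, and the issuer is inherent in the source. H9 rests on counts and refund amounts, and H10 on the auditors' own judgements of severity. Nothing suggests that the assistant regrades them. This stands: for H9 and H10 the fault is a false statement about the design, and no bias is shown.

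A second reply is that Additional file 2, which is not shown, may say who extracted what and in which order. That is fair for the carry-over question, and silence on it in an article is no fault in itself. It does not rescue the unqualified claim, because no division of labor makes the extraction of an audit report blind.

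A reader might also infer more than the article supports:

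- *That the compliance outcomes were unblinded.* Neither one assistant nor any order is stated.
- *That the reports reveal the arm of all 85 municipalities.* The two that could not be audited and the possible extra state audits rule this out.
- *That H7 was coded by judgement.* The only example given is whether a web page exists, recorded with a predefined instrument. Administrative files also show whether municipalities report to the Federal Treasury.
- *That the inflation of the arm difference can be quantified.* The article gives no misclassification rate, so any figure would only restate its own assumption.
- *That the unblinded investigators made the direct observations.* The first mention credits them, and Blinding says: "Whereas researchers and ASF management in Mexico city are fully aware of treatment allocations". But Outcome measures itself goes on to say that a research assistant applied the instrument. The first mention reads as loose phrasing.

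**Conclusion.** The point holds in limited form. The blanket blinding statements are wrong as written for H9 and H10. This follows from the article's own description of its sources and its treatment and needs no numerical assumption.

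The reports nearly identify the assigned arm: 83 of 85 municipalities if both unaudited ones were assigned to audit and no control was audited, and 78 of 85 if five controls had extra state audits.

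Loss of blinding for H7, and possibly H8 and H14, is an open risk and not a shown fact. It depends on who did which task and in what order, and the size and direction of any bias are unknown.

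**What to change.** 1. In the abstract, Outcome measures and Blinding, limit the claim to outcomes not taken from audit reports, and say that H9 and H10 are collected with the auditor known.
2. Complete and lock the web and official-source coding for H7 and H8 before any audit report is opened, or give it to an assistant who does not extract the reports.
3. Collection was expected to end on January 30, 2013, and Trial status says that analysis is under way. If an order can no longer be imposed, report who coded what and when, and claim blinding only where it held.
4. Align the phrase that credits direct observations to the investigators with the later statement that a research assistant makes them.

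The cost is a few sentences of corrected wording and, if collection is still open, an ordering rule. No extra staff are needed for the ordering option; separating the tasks needs a second assistant, and the plural in the abstract and Blinding suggests that one was available.
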